### Outcome measures

#### Primary outcome

The primary outcome measure is the change in functional and cognitive status and the change of quality of life during the study period. The functional capacity of patients will be evaluated by the Short Physical Performance Battery (SPPB) (Annex 1), which combines balance, gait ability and leg strength using a single tool. The total score will range from 0 (worst) to 12 points (best). The SPPB test has been shown to be a valid instrument for screening frailty and predicting disability, institutionalization and mortality. The magnitude of meaningful change was a one-point change in the score which has clinical relevance. If the total score is less than 10, it indicates frailty and a high risk of disability and falls.

The capacity will be assessed with the Mini-Mental State Examination (MMSE) (Annex 2). This examination is composed of seven categories designed to assess specific cognitive functions: orientation to time (5 points), orientation to place (5 points), registration of three words (3 points), attention and calculation (5 points), recalling the three words (3 points), language (8 points) and constructive visual capacity (1 point).

The MMSE score ranges from zero to 30 points, and lower values indicate possible cognitive deficit. Values from 27 to 30 denote preserved cognitive functions; from 24 to 26, changes that do not suggest deficit; from 20 to 23, changes that suggest cognitive deficit. Scores from 20 to 26 represent mild cognition impairments; between 11 and 20, moderate cognition impairment; and scores under 10 represent severe cognition impairments.

Changes in quality of life will be assessed by EuroQol-5D-VAS (Annex 3). This is a generic health status questionnaire, consisting of five dimensions (mobility, self-care, usual activities, pain/ discomfort, anxiety/depression) including three responses. It also includes a visual analogue scale for recording an individual’s rating of their current health-related quality of life (scale 0 to 100).

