**Methods/design:**

This study is a randomized clinical trial, simple blinded, conducted in the Department of Surgery of a tertiary public hospital in Navarra (Hospital Universitario de Navarra), Spain. Patients >  = 70 years old undergoing urgent abdominal surgery who meet inclusion criteria will be randomly assigned to the intervention or control group. The intervention will consist of a multicomponent physical training programme, which will include progressive and supervised endurance, resistance and balance training for 4 weeks, twice weekly sessions with a total of 8 sessions, and the group control will receive the usual care. The primary outcome measure is the change in functional (SPPB) and cognitive status (Mini-Mental State Examination) and the change of quality of life (EuroQol-5D-VAS) during the study period. The secondary outcomes are postoperative complications, length of stay, delirium, mortality, use of health resources, functional status (Barthel Index and handgrip strength tests), cost per quality-adjusted life year and mininutritional assessment. The data for both the intervention group and the control group will be obtained at four different times: the initial visit during hospital admission and at months 1, 3 and 6 months after hospital discharge.

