To reduce functional decline in older adults undergoing elective surgery, multimodal rehabilitation programmes ERAS (Enhanced Recovery After Surgery) have been designed. Several previous studies have included supervised exercises as multimodal rehabilitation; these programmes aim to promote postoperative recovery in elective surgery. They have subsequently been extrapolated to urgent surgery proving that once adapted they are effective [19–21].

Focusing on the elderly patient undergoing surgery, the functional recovery is severely affected in the subgroup of patients who have required urgent surgery and in those with post-surgical complication [16, 17, 22]. In urgent surgery patients, prehabilitation programme cannot be performed, although post-surgical rehabilitation is feasible. Rehabilitation based on physical exercise during admission in elderly patients after an acute process has shown an earlier recovery of their baseline functional status [23–28]. However, there are few recommendations for rehabilitation programmes including physical activity in older patients after urgent surgery.

We developed the first randomized clinical trial to assess the effectiveness of a rehabilitation programme based on physical exercise during the first month after surgery.

The main objective of this study is to analyze whether postoperative physical rehabilitation in a short period of time improves functional and cognitive recovery and long-term quality of life (6 months) in elderly adults undergoing urgent abdominal surgery.

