### Sample size and statistical analysis

Assuming a type I error of 0.05, a correlation between pre and post-intervention values of the Short Physical Performance Battery (SPPB) of *r* = 0.6 and a standard deviation for the SPPB of 2.5, the required sample size to detect with a power of 90% a minimum difference of 1 point between groups in the change of SPPB score is 87 patients per group [27]. Assuming losses of 20%, the final objective of the size of each group is 109 patients, and, consequently, a total sample size will be 218 subjects. For the estimation, an ANCOVA method for the analysis of the differences has been considered. The outcome variables will be analyzed using mixed models, without missing data imputation. If the proportions of missing data are very large (more than 40%) on important variables, then trial results will be considered as hypothesis-generating results.

Baseline values will be compared by group using descriptive statistics as mean and standard deviation or median and interquartile range for quantitative variables and frequencies and percentages for categorical ones. To determine the efficacy of the intervention in the quantitative variables, such as the SPPB, we will use ANCOVA models, using post-intervention value as dependent variable, group study as the principal effect and pre-intervention value as covariate. If relevant group differences were observed at baseline, we would adjust for these variables in the model. In the case of qualitative or categorized variables (such as whether an improvement of a given magnitude between pre and post-intervention has been achieved or not), comparisons between groups will be conducted with the chi-square test or Fisher’s test, and complemented with logistic regression if additional adjustment is needed.

The level of statistical significance will be 0.05. Data will be analyzed using an intention-to-treat approach and using SPSS and R statistical software.

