#### Secondary outcome measure

Postoperative complications: Clavien Dindo (Annex 4) and Comprehensive Complication Index (Annex 5)Length of stayDelirium: Confusion Assessment Method (CAM) (Annex 6)Mortality: number of days alive after admission to the hospitalUse of health resources: new admission to the hospital, admission to nursing homes and visits to the general practitionerFunctional status: Barthel index (Annex 7)Cost per quality-adjusted life year: both direct and indirect study participant costsMininutritional Assessment short form (MNA) (Annex 8)Handgrip strength test

Surgeons and physiotherapists will help participants to fill in the questionnaires. The information in both groups is obtained in a face-to-face consultation in four different stages: the initial visit and at months 1, 3 and 6 after hospital discharge. The questionnaires and tests are easy to perform, and the studio staff is qualified to perform them in a homogeneous way. The scales that we used to evaluate functional capacity [32, 33], mental state [34], quality of life [35] and nutritional status [36] have been validated for use in Spain.

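### Three outcomes are called primary with no primary visit and no success rule, while the 218 patients are sized for SPPB alone at 0.05; depending on the rule, either the 5% error or the 90% power is not assured

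*Protocol article*

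**What the plan says.** - **Primary outcome.** Under Outcome measures: "The primary outcome measure is the change in functional and cognitive status and the change of quality of life during the study period". The Methods/design paragraph of the Abstract attaches the instruments: "the change in functional (SPPB) and cognitive status (Mini-Mental State Examination) and the change of quality of life (EuroQol-5D-VAS) during the study period".
- **Visits.** Data are collected at "the initial visit and at months 1, 3 and 6 after hospital discharge", and the assessment table marks all three scales at every visit. No visit is singled out for the primary comparison.
- **Objective.** The last paragraph of the Background asks whether rehabilitation "improves functional and cognitive recovery and long-term quality of life (6 months) in elderly adults undergoing urgent abdominal surgery". Function, cognition and quality of life are joined, and the six months stands next to quality of life.
- **Sample size.** Sample size and statistical analysis begins "Assuming a type I error of 0.05" and takes an SPPB standard deviation of 2.5, a pre/post correlation of 0.6 and 90% power. It concludes that the number needed to detect "a minimum difference of 1 point between groups in the change of SPPB score is 87 patients per group". With 20% losses this becomes 109 per group, 218 in all. No standard deviation or target difference is given for MMSE or EuroQol.
- **Testing.** The same section says once: "The level of statistical significance will be 0.05". It names mixed models for the outcome variables and also ANCOVA on a single post-intervention value, without saying which visit supplies that value.

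**The concern.** The primary endpoint defines what counts as a positive trial. Here that definition is a set of three scales over a follow-up with three visits, and the sample size belongs to one scale in one pre/post comparison. The stated 5% error and 90% power both hold if SPPB at one visit is the sole primary endpoint, but the outcome section says otherwise.

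Without a rule, two readers could draw opposite conclusions from the same results, for instance if SPPB improves and MMSE does not. The risk is sharper because patients know their group (Randomization and blinding) and EQ-VAS is their own rating. A win on any one of the three could therefore rest on the scale most open to expectation.

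**Working it through.** **1. The plan's own figure**

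Inputs from Sample size and statistical analysis: SD 2.5, r = 0.6, difference 1 point, type I error 0.05, power 90%, ANCOVA. Sidedness is not stated; two-sided is assumed.

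- Residual SD = 2.5 × √(1 − 0.6²) = 2.0.
- n per group = 2 × (1.960 + 1.282)² × 2.0² / 1² ≈ 84.1, so 85. The plan has 87, which agrees within 2 patients. One-sided ANCOVA would give 69, so two-sided fits.
- Power at 87: 1 / (2.0 × √(2/87)) = 3.298; Φ(3.298 − 1.960) = 0.910 (0.906 by noncentral t).
- 87 / 0.8 = 108.75, so 109 per group and 218 in total.

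The SPPB calculation is sound for what it claims.

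**2. Rule A: any one of the three scales suffices, each at an unadjusted 0.05**

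Independent tests: 1 − 0.95³ = 14.3%. Correlated tests were simulated with 400,000 multivariate normal draws. The documents give no between-scale correlation, so a range is assumed.

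| Between-scale correlation | Familywise error |
|---|---|
| 0 | 14.3% |
| 0.3 | 13.7% |
| 0.5 | 12.6% |
| 0.7 | 10.9% |

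Power does not suffer: the chance of at least one win is no lower than SPPB's own 0.91, and is 0.97 or more if all three scales have the same standardised effect.

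**3. Worst case of Rule A: nine separate scale-by-visit tests**

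Independent: 1 − 0.95⁹ = 37.0%. With assumed between-visit correlation 0.5–0.8 and between-scale correlation 0–0.7, it is about 20–33%. The unnamed visit matters even for one scale: any of three visits gives about 10–13% over the same between-visit range.

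**4. Rule B: all three scales must succeed, each at 0.05**

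The type I error stays at or below 5%. Power cannot exceed that of SPPB alone (0.91), so it stays near 90% only if MMSE and EQ-VAS are almost certain to succeed. If they have the same standardised effect as SPPB (an assumption), power at 87 per group is:

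- correlation 0: 0.910³ ≈ 0.75
- correlation 0.5: 0.80
- correlation 0.7: 0.83

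Restoring 90% under independence needs 0.90^(1/3) = 0.965 for each scale: 115 evaluable per group, 144 after losses, 288 in total.

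**5. Rule C: Bonferroni over three scales**

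Alpha is 0.05/3 = 0.0167. SPPB power at 87 per group falls to 0.82 by the normal approximation, 0.81 by noncentral t. Restoring 90% needs 109 evaluable per group, 137 after losses, 274 in total.

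**6. Rule D: SPPB at one named visit, the others ordered after it**

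Alpha stays at 0.05, SPPB power at about 0.91, and the total at 218.

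**The case against.** The strongest reply is that this is a condensed article. Alpha allocation and testing order are commonly left to an analysis plan, which may exist. That stands for the detail of a multiplicity procedure. It does not cover the choice of primary outcome and time point, which belongs in the protocol and which this article makes: three scales over the whole study period. An alpha split placed elsewhere would also clash with a sample size that gives the full 0.05 to SPPB.

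It is also fair to say that the 90% is openly tied to SPPB and can be reproduced. So the power statement is not wrong; it simply does not reach the other two primary outcomes.

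Four stronger readings are tempting, and the text does not support them.

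- **That the trial has neither 5% error nor 90% power.** No single unadjusted rule on the three scales breaks both. Rule A inflates the error and leaves power at or above 0.91; Rule B controls the error and loses power.
- **That each scale is tested at 0.05.** This is an inference from one general sentence.
- **That nine tests are planned.** A mixed model can give one test per outcome, and the ANCOVA text speaks of one post-intervention value. The 20–33% is a worst case.
- **That EuroQol adds another primary choice.** The outcome is consistently labelled EuroQol-5D-VAS. Describing both parts of the instrument is at most loose wording.

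**Conclusion.** The point holds in this form: the primary endpoint is badly fixed, and the sample size matches only one of its three parts. With no rule stated, either the 5% error is not assured (about 11–14% if any scale suffices) or the 90% power is not assured (about 75–83% if all must succeed). No power can be worked out from the article for MMSE or EQ-VAS.

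The error range rests on assumed between-scale correlations of 0 to 0.7 and on unadjusted testing at 0.05. The power range rests on those correlations and on equal standardised effects. The conclusion that one of the two properties is unsecured does not depend on the exact values. It should be settled before results by group are seen, because the criterion for success is otherwise open to choice afterwards.

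**What to change.** Before any unblinded look at the data:

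1. Name SPPB at one stated visit as the single primary endpoint. Month 1 would suit the pre/post basis of the sample size; month 6 would suit the long-term objective. The documents do not settle this. Visits are counted from discharge and make-up sessions are allowed, so the investigators should confirm where the chosen visit falls relative to the end of the programme.
2. Name the same visit as the ANCOVA post-intervention value or as the mixed-model contrast, and say which of the two models is primary.
3. Test the remaining outcomes in a pre-stated fixed sequence at two-sided 0.05, or report them as secondary estimates with 95% confidence intervals. The order of MMSE and EQ-VAS is for the investigators to choose.
4. State that no power is claimed for MMSE or EQ-VAS.

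The cost is a protocol amendment and a registry update, with no extra patients. The price is that cognition and quality of life become ordered secondary claims. If the investigators want all three as primary, they should state the rule and re-size: 274 patients for a Bonferroni split that keeps 90% power on SPPB, or 288 for all three to succeed under independence and equal standardised effects.

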#### Secondary outcome measure

Postoperative complications: Clavien Dindo (Annex 4) and Comprehensive Complication Index (Annex 5)Length of stayDelirium: Confusion Assessment Method (CAM) (Annex 6)Mortality: number of days alive after admission to the hospitalUse of health resources: new admission to the hospital, admission to nursing homes and visits to the general practitionerFunctional status: Barthel index (Annex 7)Cost per quality-adjusted life year: both direct and indirect study participant costsMininutritional Assessment short form (MNA) (Annex 8)Handgrip strength test

Surgeons and physiotherapists will help participants to fill in the questionnaires. The information in both groups is obtained in a face-to-face consultation in four different stages: the initial visit and at months 1, 3 and 6 after hospital discharge. The questionnaires and tests are easy to perform, and the studio staff is qualified to perform them in a homogeneous way. The scales that we used to evaluate functional capacity [32, 33], mental state [34], quality of life [35] and nutritional status [36] have been validated for use in Spain.

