## Methods/design

### Study design

This study is a parallel group, two-arm, superiority randomized trial with 1:1 allocation ratio, is monocentric and is conducted in the Department of Surgery of a tertiary public hospital in Navarra (Hospital Universitario de Navarra), Spain. Patients undergoing urgent abdominal surgery who meet inclusion criteria will be randomly assigned to the intervention or control group.

Patient recruitment will begin in 4 days after the surgical procedure, and these patients will be identified through the list of patients admitted to the hospital and assigned to the Department of General Surgery. Prior to randomization, the investigators will review the contraindications to participate in the exercise programme and will provide general information about the study. After signing an informed consent form, the subjects will be chosen randomly. 

Randomization will be performed by applying http://www.randomizer.org/. The doctor who decides the inclusion in the intervention or control group will not be the attending physician. Patients will be informed of the random inclusion in one of the groups.

The information in both groups is obtained in four different stages: the initial visit and at months 1, 3 and 6 after hospital discharge.

The protocol employs relevant standard protocol items for clinical trials according to the SPIRIT 2013 statement [29] and follows the CONSORT statement [30] for transparent reporting.

The trial is registered at ClinicalTrials.gov, identifier NCT05290532.

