**Table Taba:** 

Assessments	During hospital admission	1 month	3 months	6 months
**SPPB**	X	X	X	X
**Handgrip strength test**	X	X	X	X
**MMSE score**	X	X	X	X
**EuroQol-5D-VAS**	X	X	X	X
**Barthel Index**	X	X	X	X
**Mininutritional assessment short form**	X	X	X	X
**Confusion assessment method**	X			
**Clavien Dindo**	X	X		
**Comprehensive Complication Index**	X	X		
**Length of stay**	X			
**Use of health resources**		X	X	X
**Mortality**	X	X	X	X

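### Mortality is counted as days alive from admission, before randomisation, with follow-up ending at a discharge-based visit; complications and delirium have no start point after randomisation

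*Protocol article*

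**What the plan says.** All references are to the protocol article.

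- **Mortality.** Under Secondary outcome measure: "Mortality: number of days alive after admission" to the hospital.
- **Randomisation.** Under Study design: "Patient recruitment will begin in 4 days after the surgical procedure", and then "After signing an informed consent form, the subjects will be chosen randomly". Allocation therefore follows admission, surgery and consent.
- **Follow-up.** Data are collected at "the initial visit and at months 1, 3 and 6 after hospital discharge". The Abstract places the first of these in hospital: "the initial visit during hospital admission and at months 1, 3 and 6 months after hospital discharge".
- **Complications.** Listed as "Postoperative complications: Clavien Dindo (Annex 4) and Comprehensive Complication Index (Annex 5"). The assessment table marks both scales in the admission column and again at 1 month.
- **Delirium.** The row "Confusion assessment method" is marked only under "During hospital admission".
- **Length of stay.** Marked in that same column only, with no start point given.

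The Background places the programme in the first month after surgery, and Detail description gives 4 weeks and 8 sessions. Neither says whether training starts before or after discharge.

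**The concern.** An outcome in a randomised comparison should start when the arms start to differ. The mortality count starts earlier, at admission. Nobody can die between admission and randomisation and still be in the trial, so those days are alive time by construction and allocation cannot affect them.

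The end of the count is also a problem. Because the last visit is timed from discharge, the observation window gets longer with the hospital stay. A plain day count then mixes survival with stay. A programme that shortened stay and left survival unchanged would appear to shorten life slightly.

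For complications and delirium the issue is milder. With no stated start after randomisation, events that preceded allocation would normally be counted. They are balanced between arms in expectation, so the cost is a diluted effect and lost power.

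**Working it through.** **The plan's own figure.** The sample size is not in question, but 109 per arm is used below. ANCOVA SD = 2.5 × √(1 − 0.6²) = 2.0. n = 2 × [2.0 × (1.96 + 1.2816)]² / 1² = 84.06, so 85 per group (86 with the t distribution), against 87 stated. 87 / 0.8 = 108.75, so 109, and 2 × 109 = 218. The figures reproduce closely.

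**Days alive for a survivor.** Let S be the total stay and R the day of randomisation, both counted from admission. Take 6 months as 182 days. The documents give no stay, so S is a range.

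- As defined: S + 182. For S = 7, 10, 20 and 30 this is 189, 192, 202 and 212 days.
- Start moved to randomisation, end left at the last visit: (S − R) + 182. This still grows with the stay after randomisation.
- Start at randomisation, fixed horizon: 182 for every survivor, whatever the stay.

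Moving the start alone is therefore not enough.

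**Size if stay differs by 2 days and survival does not.** Assumed: 12% mortality in both arms; mean stays of 14 and 12 days.

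- Survivors contribute 0.88 × 2 = 1.76 days. If the death times of the other 12% also shift by the full 2 days, the total is 1.76 + 0.12 × 2 = 2.0 days. The shift is about 1.8 to 2.0 days.
- For scale, set a survivor's count at 14 + 182 = 196 and spread deaths evenly over 0 to 196 days (a simplification).
- Mean = 0.88 × 196 + 0.12 × 98 = 184.2.
- Variance = 0.88 × (196 − 184.2)² + 0.12 × [(98 − 184.2)² + 196²/12] ≈ 1,400, so the SD is about 37.
- SE of the difference = 37 × √(2/109) ≈ 5.
- The shift is about 1% of the mean and 0.35 to 0.4 SE.

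**Dilution of an event outcome.** Let p be the control risk, f the share of control-arm events before randomisation, and RR the true risk ratio afterwards. The observed ratio is f + (1 − f) × RR. Assumed: p = 30%, RR = 0.6, 109 per arm, two-sided 5%.

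| f | Observed RR | Power, all events | Power, post-randomisation events only |
|---|---|---|---|
| 0 | 0.60 | 0.55 | 0.55 |
| 0.25 | 0.70 | 0.33 | 0.41 |
| 0.50 | 0.80 | 0.17 | 0.27 |
| 0.75 | 0.90 | 0.07 | 0.15 |

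At f = 0.50, control risks of 20% and 40% give 0.12 against 0.19 and 0.23 against 0.36. The fair comparison is across a row. The fall down the last column reflects fewer events that allocation can affect, which no redefinition recovers.

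**The case against.** A reader might infer that all four outcomes (mortality, stay, complications and delirium) are counted from admission. The article says so only for mortality. Complications are postoperative by name, so they run from surgery, and they are recorded again at 1 month, so part of their window falls after allocation. Stay and delirium have no stated origin.

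A reader might also infer that delirium is simply a baseline variable, because the CAM shares a column with the baseline SPPB. The same column holds length of stay and mortality, which cannot be known at a visit before randomisation, so it may cover the whole admission. The participant flow and schedule figures, which could settle this, are not available here. The text is ambiguous and does not show that delirium can reveal only chance differences.

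Nor does the article commit days alive to ANCOVA with a baseline value. Its statistical section also names mixed models for the outcome variables and introduces ANCOVA with the SPPB as its example. A censored survival method could properly sit in a separate analysis plan and would remove the reward for longer stays.

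Finally, the directional effect needs the programme to alter stay. If training starts only after discharge, that premise largely fails. Total stay is also a conventional measure and a valid randomised comparison.

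These points narrow the concern. They do not change the printed mortality definition, which starts before allocation, or the last visit, whose date moves with stay.

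**Conclusion.** The point holds for mortality as stated, and for complications and delirium on their ordinary reading. The mortality count includes survival time guaranteed by being randomised, and a survivor's total rises one day per extra hospital day. A bias between arms follows only if the programme changes stay and the count is analysed without censoring. On the assumed 2-day difference in stay and 12% mortality it is about 1.8 to 2.0 days, small against a standard error of about 5.

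For complications and delirium the consequence is dilution, not a bias towards either arm. If half the events preceded allocation, a true ratio of 0.60 would be seen as 0.80, and power would be 0.17 where counting later events alone would give 0.27 (at the assumed 30% risk).

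The stays, mortality, event risks and share of early events are all assumptions; the article gives none. Only secondary outcomes are touched.

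**What to change.** 1. **Mortality:** define it as time from randomisation to death, up to a fixed horizon such as 6 months after randomisation, censored at last contact. Any standard method that respects censoring will do.
2. **Complications and delirium:** count as outcomes only events with onset after randomisation, and record earlier events as baseline covariates.
3. **CAM:** state when it is done relative to randomisation. If it is done only at an initial visit before randomisation, report it as a baseline characteristic. If it is repeated through the admission, keep delirium as an outcome under item 2.
4. **Stay:** report days from randomisation to discharge alongside total stay. State whether training begins before or after discharge, so that readers can judge whether stay could respond to it.

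The cost is mainly wording. Admission, randomisation, discharge and death dates should already be on record, and onset dates for complications and delirium need to be captured or read from the notes. If randomisation takes place in hospital, 6 months after randomisation falls no later than the existing last visit, so no extra contact is needed. The price is fewer countable events for complications and delirium, but those dropped are ones allocation could not have affected.
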